## Abstract

**Introduction:**

Cerebral palsy (CP) is a posture and movement disorder and different therapeutic modalities, such as the use of braces, have sought to favor selective motor control and muscle coordination in such patients. The aim of the proposed study is to determine the effect of the combination of posture-control insoles and ankle-foot orthoses (AFOs) improving functional limitation in children with CP.

**Methods/Design:**

The sample will be composed of 24 children with CP between four and 12 years of age. After the signing of the statement of informed consent, the children will be randomly allocated to two groups: a control group using AFOs alone and an experimental group using both posture-control insoles and AFOs. Evaluations will be performed on five occasions: without any accessory (insoles or AFOs), immediately after, one month after, six months after and one year after AFOs or insole and AFOs use. The evaluation will involve the analysis of gait, static and functional balance, mobility and hypertonia. The three-dimensional assessment of gait will involve the eight-camera SMART-D SMART-D 140® system (BTS Engineering), two Kistler force plates (model 9286BA) and an eight-channel, wireless FREEEMG® electromyography (BTS Engineering). Static balance will be assessed using a Kistler force plate (model 9286BA). Clinical functional balance and mobility will be assessed using the Berg Balance Scale, Timed Up-and-Go Test and Six-Minute Walk Test. The posture-control insoles will be made of ethylene vinyl acetate, with thermal molding for fixation. The fixed orthoses will be made of polypropylene and attached to the ankle region (AFO). The results will be analyzed statistically, with the level significance set to 5% (p < 0.05).

**Trial Registration:**

Trial Registration Number: RBR6d342s (http://www.ensaiosclinicos.gov.br/news/)

## Introduction

Cerebral palsy (CP) is a permanent but not immutable posture and movement disorder resulting from a non-progressive cerebral disorder due to hereditary factors or events occurring during pregnancy, child birth, the neonatal period or in the first days of life, leading to limited motor activity and often accompanied by sensory, cognition, communication, perception and behavioral disorders. [1] The most current definition states that CP is a chronic, non-progressive disease with movement, posture and motor function disorders stemming from lesions or abnormalities in the immature brain [2].

Motor impairment is the major manifestation of CP, with consequent changes in bodily biomechanics. Moreover, children with CP may exhibit intellectual, visual and hearing disorders, which, when added to motor impairment and both task and environment restrictions, affect functional performance in a variety of different ways [3,4].

Neuromotor impairment in this disease involves different parts of the body, resulting in specific topographic classifications, such as quadriplegia, hemiplegia and diplegia [5]. However, children with CP are currently classified based on functionality, which encompasses the functions of the body, activities and social participation. The Gross Motor Function Classification System for Cerebral Palsy (GMFCS) [6] classifies children with CP based on age (0–2, 2–4, 4–6 and 6–12 years) and respective functional levels. Children classified as Level I can walk without restrictions, but tend to be limited in more advanced motor skills, whereas children classified as Level V are very limited in their ability to walk, even with a gait-assistance device [7]. The GMFCS is an extremely important tool for physical therapists who work with children with CP, as it allows the establishment of adequate therapeutic goals based on the patient’s age and motor level [7,8].

Functional mobility can also be assessed using the Berg Balance Scale and the Timed Up-and-Go Test. These scales allow a quantitative assessment of functional balance.

With regard to gait, a three-dimensional analysis allows a detailed evaluation of the kinetic, kinematic and electromyographic aspects of each phase of the gait cycle and is an important tool for the assessment of the results of clinical interventions in children with CP, who exhibit functional limitations due to excessive muscle weakness, abnormal joint kinetics and abnormal postural reactions [9].

Different therapeutic interventions seek to improve selective motor control and muscle coordination in these patients. The use of an orthosis (brace) is one such method, the aim of which, according to Lucarelli et al. (2007), is to improve the gait pattern [10]. Different types of orthosis may be prescribed, such as an ankle-foot orthosis (AFO), which assists in the alignment and quality of ambulation. This type of brace provides a reduction in plantar flexion of the ankle during initial contact with the ground, which leads to greater stability in the stance phase [11].

Similarly, the aim of posture-control insoles is to reorganize the tonus of muscle chains and influence body posture through correction reflexes. These insoles affect muscle proprioception, leading to changes in the ascending proprioceptive chains [12]. According to Gagey & Weber (2000), [13] the stimulation of specific regions of the sole of the foot leads to a change in postural tonus and a repositioning of the pelvis and muscle asymmetries along the spinal column. Postural reprogramming occurs when mechanoreceptors in the plantar region are activated by deformation of the skin due to the topographic relief of the support surface, as occurs with posture-control insoles [14].

The aim of the proposed study is to determine the effect of the combination of posture-control insoles and ankle-foot orthoses (AFOs) on functionality in children with CP. The hypothesis is that posture-control insoles lead to a change in sensitive afference, thereby stimulating a new postural reaction that favors better biomechanical alignment and allows greater efficiency in functional tasks, especially those related to locomotion and balance.

## Methods

### Type of study

A randomized, controlled, clinical trial will be carried out.

In compliance with Resolution 196/96 of the Brazilian National Health Council, the proposal was sent for the analysis of the Human Research Ethics Committee and received approval (August 8, 2011).

The children will participate on a volunteer basis and legal guardians will sign a statement of informed consent.

### Sample description and characterization

The sample size will be calculated based on the study carried out by Buckon et al. (2004)[15] with results on gait cadence in children with CP (GMFCS Levels I and II) with and without a fixed AFO. For an expected size effect of 17 steps/minute, with a standard deviation of 15 steps/minute and assuming an α risk of 0.05 and an 80% power, the sample was estimated at 12 children per group. Thus, the sample will be composed of 24 male and female children with CP aged four to 12 years**.**

The participants will be recruited and selected for eligibility based on the criteria listed below.

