### Sample composition

After fulfilling the eligibility criteria, the children will be randomly divided into two groups: 1) a control group that will make use of AFOs exclusively and 2) an experimental group that will make use of AFOs combined with posture-control insoles.

Children in therapy at rehabilitation centers will be recruited and instructed to maintain their normal therapy throughout the study. Randomization with involve a series of sealed opaque envelopes to ensure confidentiality. Each envelop will contain a card stipulating to which group the child will be allocated.

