### Statistical analysis

The Kolmogorov-Smirnov test will be used to test the data with regard to Gaussian distribution. Central tendency and dispersion measures will be expressed as mean and standard deviation values or median and inter-quartile interval when exhibiting parametric and non-parametric distribution, respectively. Either repeated-measure ANOVA or Friedman’s test will be used for the intra-group analysis and either one-way ANOVA or the Kruskal-Wallis test will be used for the inter-group analysis for data with parametric and non-parametric distribution, respectively. The data will be organized and tabulated using the Statistical Package for the Social Sciences (SPSS v.19.0). The level of significance will be set to 5% (p < 0.05).

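### On the article's own inputs, 12 children per group give about 76% power for the planned two-group ANOVA, not the stated 80%; 14 per group would be needed

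*Protocol article*

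**What the plan says.** The section on sample description and characterization takes its planning values from an earlier study of gait cadence in children with CP, with and without a fixed AFO:

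- Effect: "For an expected size effect of 17 steps/minute".
- Variability: "with a standard deviation of 15 steps/minute".
- Error rates: "assuming an α risk of 0.05 and an 80% power".
- Result: "80% power, the sample was estimated at 12 children per group".
- Enrolment: "Thus, the sample will be composed of 24 male and female children with CP aged four to 12 years".

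The section names no formula. It does not say whether the calculation is one- or two-sided, or whether the SD is between children or of within-child differences. The number enrolled equals twice the calculated number per group.

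Under Sample composition, "the children will be randomly divided into two groups". Under Statistical analysis, at a 5% level, "either one-way ANOVA or the Kruskal-Wallis test will be used for the inter-group analysis", the choice depending on whether the data are judged Gaussian. Under Procedures, evaluations run to one year.

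**The concern.** The 80% figure is the only quantitative justification for enrolling 24 children. It is a claim about the comparison that will be made, and for two groups that comparison is a t-test with 22 degrees of freedom. A normal approximation is optimistic at that size, and rounding 12.22 down instead of up adds to the optimism.

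If true power is about 76%, the chance of missing a real difference of 17 steps/minute is 24.4% rather than the stated 20%. A null result would then be read against a false-negative risk that the design does not meet, even when every planning value is correct and every child is analysed.

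**Working it through.** **Inputs.** Difference 17, SD 15, alpha 0.05, power 80% and 12 per group come from the sample-size section. The two-group one-way ANOVA comes from the Statistical analysis and Sample composition sections. I take the SD as between children, which is what a between-group test uses. I take the test as two-sided, which the ANOVA F-test implies for two groups.

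Standardised difference: d = 17/15 = 1.133.

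**1. Reproducing the article's 12.** Two-sided normal approximation:

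n per group = 2 × (1.960 + 0.842)² × (15/17)² = 12.22

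Rounded up, as needed to reach the target, this is 13. Rounded down it is the stated 12. Power at 12 by the same formula is Φ(1.133 × √(12/2) − 1.960) = Φ(0.816) = 79.3%.

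**2. Other routes to 12.** A one-sided alpha of 0.05 needs 10 per group (normal) or 11 (t), and 12 per group would then give 85.2%. A paired two-sided t-test needs 9. None of these yields 12, so step 1 is the likely source.

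**3. Power of the planned test.** With n per group, the pooled t-test has 2n − 2 degrees of freedom and noncentrality d × √(n/2). At n = 12 there are 22 degrees of freedom, the critical value is 2.074 and the noncentrality is 1.133 × √6 = 2.776. Exact results from the noncentral t (the ANOVA F calculation gives the same 75.6% at 12):

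| Analysed per group | Power |
|---|---|
| 10 | 66.9% |
| 11 | 71.5% |
| 12 | 75.6% |
| 13 | 79.2% |
| 14 | 82.3% |

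Solving for 80% gives 13.25, so 14 per group (28 in total). The rows for 10 and 11 illustrate loss only; the article gives no loss rate.

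**4. Sensitivity to rounding of the inputs.** Letting the effect run from 16.5 to 17.49 and the SD from 14.5 to 15.49, exact power at 12 per group runs from about 70% to 81%.

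**5. Baseline-adjusted alternative at 12 per group.** Adjusting for baseline cadence with correlation r divides the residual SD by a factor 1/√(1 − r²), so the noncentrality becomes 2.776/√(1 − r²), with 21 degrees of freedom. The article gives no r, so a range is shown:

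| r (assumed) | Power |
|---|---|
| 0.2 | 77% |
| 0.3 | 79% |
| 0.4 | 82% |
| 0.5 | 86% |
| 0.6 | 91% |

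The adjustment reaches 80% only when r is somewhat above 0.3.

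**The case against.** The strongest reply is that this is not a wrong calculation. The standard formula on the stated inputs gives 12.22, and 12 per group has 79.3% power by that formula. What remains is a rounding choice and a missing small-sample correction, for planning values that are themselves whole-number guesses. This largely stands: it explains where 12 came from and limits the seriousness of the point. It does not make 80% true for the planned test, and even the lenient formula falls just short.

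It can also be said that the article states neither sidedness nor the type of SD, and that one-sided power at 12 would exceed 80%. This stands as a caveat. The planned F-test is what supports the two-sided reading.

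Three stronger readings are tempting, and the article does not support them:

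- *That the Kruskal-Wallis option lowers power further.* The article reserves that test for data judged non-Gaussian. Its loss against ANOVA under normality is small (about 74% against 75% in simulation at 12 per group). In simulated heavy-tailed or skewed data with the same standardised shift it did better: about 82% against 76% for Laplace data and 88% against 78% for exponential data.
- *That all 24 children are assumed to be analysable.* The article says only that the sample will comprise 24. It shows no allowance for loss, but a fuller protocol may deal with that.
- *That loss over one year reduces power by a known amount.* No loss rate is given, and the calculation is not tied to the one-year visit. Only the direction is certain.

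**Conclusion.** The point holds in a limited form. The stated 80% is not delivered on the article's own inputs: the planned two-group ANOVA has about 76% power at 12 per group, and at least 80% needs 14 per group. The gap is 4.4 percentage points, or four children in total, and comes from a normal approximation rounded down.

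The result rests on a two-sided test and on SD 15 being between children. Since rounding of the inputs alone can move power between about 70% and 81%, the figure should be quoted as about 76% and not to a decimal place. This is a modest misstatement that should be corrected; it does not show that the design is unsound.

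**What to change.** Replace the power statement with wording such as: *12 children per group give about 76% power (two-sided, one-way ANOVA/t-test, alpha 0.05) for a difference of 17 steps/minute with a between-child SD of 15.* This costs one sentence and a slightly less favourable figure. Any power quoted for fewer analysed children should be labelled as resting on an assumed loss.

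Alternatively, keep 24 children, make a baseline-adjusted comparison the planned between-group test, and state its power with the assumed correlation and the range shown above. An evaluation before insole use is already scheduled, so this needs no extra children or visits. It does change the planned analysis, and at a correlation of 0.3 or below it would still miss 80%.

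Keeping both the 80% target and the unadjusted ANOVA would take 28 children, four more than planned.

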### Inclusion criteria

Diagnosis of CP; classification in Levels I and II of the GMFCS; and independent ambulation with no need for gait assistance devices (walker or crutches).

### Exclusion criteria

History of surgical procedures or application of phenol in previous 12 months; history of neurolytic blocks in previous six months; cognitive or visual impairment that might impede the performance of the tasks; ankle deformities not reducible to zero; and obesity [16].

### Sample composition

After fulfilling the eligibility criteria, the children will be randomly divided into two groups: 1) a control group that will make use of AFOs exclusively and 2) an experimental group that will make use of AFOs combined with posture-control insoles.

Children in therapy at rehabilitation centers will be recruited and instructed to maintain their normal therapy throughout the study. Randomization with involve a series of sealed opaque envelopes to ensure confidentiality. Each envelop will contain a card stipulating to which group the child will be allocated.

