### Procedures

The children selected (whose legal guardians agreed to their participation by signing a statement of informed consent) will be evaluated regarding their anthropometric data and GMFCS classification and randomly allocated to the experimental and control groups. The control group will make daily and constant use of the AFOs. The experimental group will make use of the posture-control insoles for six hours daily during the most active period of the day and will remain using the AFOs the rest of the day.

The evaluation process (before, immediately after, one month after, six months after and one year after insole use) will be performed under two different conditions. Under the first condition (evaluation 1), the children will not use an assistance device and under the second condition (evaluation 2), the children will use either the posture-control insoles or the AFOs, depending on the group to which they belong. Evaluation 1 and evaluation 2 will be performed by different examiners. Examiner 1 will not be aware of which group the children belong, thereby characterizing the investigation as a blind study.

The evaluations will be held on two non-consecutive days. The Berg Balance Scale, Timed Up-and-Go Test, Six-Minute Walk Test and modified Ashworth scale will be administered on the first day. The three-dimensional gait analysis and the static balance test on a pressure plate will be performed on the second day.

For the three-dimensional gait analysis, the equipment will be introduced to the children and the procedures will be explained. The children will be submitted to an initial practice gait exam to become familiarized with the procedure (no data will be collected on this training run). The children will wear bathing suits to facilitate the placement of the markers. The skin will be cleaned with alcohol for better attachment of the markers on the exact sites. The markers will be enveloped in adhesive tape lined with microscopic glass spheres and attached to a plastic base with double-sided adhesive tape. The markers will be attached to the children in the orthostatic position, as suggested by Davis et al. (1991), [28] on the following anatomic structures:

Pelvis: Three markers will be positioned on the anterior superior iliac spines (right and left) and one between the posterior superior iliac spines.

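### GMFCS level is known before allocation but enters neither the described envelope allocation nor the named between-group test; using it would be a cheap gain in precision in a trial of 24 children

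*Protocol article*

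**What the plan says.** Under Inclusion criteria the protocol article requires "classification in Levels I and II of the GMFCS", together with independent walking without a walker or crutches. Under Procedures, the children "will be evaluated regarding their anthropometric data and GMFCS classification and randomly allocated to the experimental and control groups", so the level is available when each child is allocated.

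Sample composition describes the mechanism as a series of sealed opaque envelopes: "Each envelop will contain a card stipulating to which group the child will be allocated". Strata and blocks are not mentioned. Statistical analysis names one-way ANOVA or the Kruskal-Wallis test for the comparison between groups, chosen by distribution, and names no covariate.

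The article treats GMFCS level as a measure of motor function. The Introduction calls it important for setting goals by age and motor level. Instruments adds motor growth curves, separate for each GMFCS level, with the GMFM-66 score on the vertical axis.

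The sample size rests on gait cadence in a source population that also pooled Levels I and II: "For an expected size effect of 17 steps/minute", "with a standard deviation of 15 steps/minute", giving 12 children per group.

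**The concern.** The outcomes are gait, static and functional balance, Timed Up-and-Go, Six-Minute Walk and hypertonia. Most of these measure motor function, which is what GMFCS level grades. If level predicts them, an arm that happens to receive more Level I children will tend to do better whether or not the insole works. Neither the allocation as described nor the test as named makes use of level. A reader of the results could then not easily separate a treatment difference from a difference in case mix, and the variation between levels would stay in the error term of a trial with little power to spare.

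**Working it through.** **Inputs.** From Sample description and characterization: difference 17 steps/min, SD 15, "assuming an α risk of 0.05 and an 80% power", and "the sample was estimated at 12 children per group". Sidedness is not stated; two-sided is assumed. The mix of Level I and II children is not given, so 6 to 18 Level I children out of 24 is assumed. The size of any cadence gap between the levels is not given either, so 5, 10 and 15 steps/min are assumed for illustration.

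**1. The plan's own figure.** By the normal approximation, n per arm = 2 × [15 × (1.960 + 0.842) / 17]² = 12.2. This is close to the stated 12. At 12 per arm the power is 79.3% by the normal approximation and 75.6% by the two-sided t-test.

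**2. Chance of imbalance without use of level.** Take a 12:12 split and K Level I children among 24. The number X in one arm is hypergeometric, P(X = x) = C(K, x) × C(24 − K, 12 − x) / C(24, 12), with C(24, 12) = 2,704,156. The arms differ by |2X − K| Level I children.

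For K = 12, the event of a difference of 4 or more (8 v 4 or worse) needs X ≥ 8 or X ≤ 4. The upper tail is 495² + 220² + 66² + 12² + 1² = 297,926. Doubled and divided by 2,704,156, it gives 0.220.

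| Level I children of 24 | Differ by 2 or more | Differ by 4 or more | Differ by 6 or more |
|---|---|---|---|
| 12 | 68% | 22.0% | 3.9% |
| 10 or 14 | 68% | 21.4% | 3.6% |
| 8 or 16 | 67% | 19.3% | 2.7% |
| 6 or 18 | 64% | 15.5% | 1.4% |

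If arm sizes are not forced to 12:12 (simple randomisation), the chance that the share of one level differs by 33 percentage points or more is 15% with an even mix, 12% with 8 or 16 children at that level, and 8% with 6.

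**3. What such a split does to the comparison.** A difference of 4 children in arms of 12 is 4/12 = one third. The shift in the arm difference is one third of the gap between levels.

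| Assumed gap (steps/min) | Shift | Share of the planned 17 |
|---|---|---|
| 5 | 1.7 | 10% |
| 10 | 3.3 | 20% |
| 15 | 5.0 | 29% |

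For scale, the standard error of the arm difference is 15 × √(2/12) = 6.1 steps/min, so even the largest of these shifts is less than one standard error.

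**4. What adjustment gains.** Suppose levels are evenly mixed and balanced between arms, and SD 15 is the SD over both levels together. The within-level SD is then √(225 − gap²/4), which is 14.8, 14.1 or 13.0 for a gap of 5, 10 or 15. With one degree of freedom spent (21 instead of 22), t-test power at 12 per arm rises from 75.6% to 77%, 80% or 86%. This gain does not depend on an unlucky split, and it is small if the gap is small.

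**5. What stratified blocks do.** One envelope series per level limits the arm difference within each level to 1 child with blocks of 2, or 2 children with blocks of 4. A difference of 4 can then not occur.

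**The case against.** Several stronger readings are tempting, and the documents do not support them.

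- **That the article itself describes Levels I and II as walking differently.** It says "Children classified as Level I can walk without restrictions, but tend to be limited in more advanced motor skills", but the contrast it draws is with Level V. Level II walking is never described, and every child must walk unaided. The most that can be said is that the article uses level as a measure of motor function. How far I and II differ on these outcomes is an assumption.
- **That a sizeable imbalance is likely.** A difference of 4 or more children has at most about a 22% chance, so about four trials in five or more would escape it. Only a difference of 2 or more is likely.
- **That the trial is stated to be unstratified.** The article mentions no strata; it does not exclude them. It is a condensed report, the flowchart is not shown, and such detail may stand in a fuller document.
- **That the comparison would be biased or invalid.** Under proper randomisation, chance imbalance is part of the sampling error that the test already allows for, and the type I error is kept. The planning SD also comes from a source with both levels pooled.

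It can be added that a baseline evaluation is planned, so a stable difference between arms would be visible, and that covariates are often left to an analysis plan. All of this stands, and it limits the point to one of efficiency. It does not remove it: the article names specific between-group tests, these have no place for level as named, and the variable is already being collected.

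**Conclusion.** This is a worthwhile, inexpensive improvement and not an error in the plan. As described, the trial leaves a known severity variable out of both allocation and comparison. The consequence is a 15-22% chance of a difference of 4 or more Level I children between arms. That range assumes 12:12 arms, 6 to 18 Level I children of 24, and allocation that ignores level. Such a split would shift the arm difference by 1.7 to 5.0 steps/min if the levels differ by 5 to 15, a range for which the documents give no figure. The cost is lost precision and a harder reading of one small trial. The validity of the randomised test is not in question.

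**What to change.** Replace the unadjusted between-group test with a linear model (ANCOVA) that includes group and GMFCS level; where the data are clearly non-normal, use a rank test stratified by level. This can be done whatever the state of the envelopes. If they are not yet prepared, make one series per GMFCS level in permuted blocks, with block size concealed from those who recruit, and state this under Sample composition. If stratification is already in place, say so there and carry level into the analysis.

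The cost is one degree of freedom and a second set of envelopes. Arm sizes may differ by a child or two if blocks are left incomplete.
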